### Recruitment

#### Sites

NHS Trust sites will be recruited via professional and research networks across England, derived from earlier stages of the research programme. Participating Trusts will identify teams for inclusion in the study. Purposive recruitment will seek a diverse range of team service models and service user demographics, reflecting the earlier survey work undertaken in the study [12]. Each Trust shall confirm their capacity to undertake the trial by completing the Health Research Authority Statement of Activities, constituting a formal agreement with the study sponsor.

#### TMCDs (*n*=30) and practitioners (*n*=180)

In each team an Individual Team Manager, or a delegated senior practitioner, will be briefed by the research team about the trial and provided with participant information sheets. Two practitioners in each team will be sought to act as volunteer research coordinators and allowed up to 3 days from receiving the study information to decide if they wish to participate. These staff will recruit the remaining practitioners from the team.

#### People with dementia and their carers (*n*=450)

People with dementia and their carers will be identified from new referrals to the team’s caseload. Team practitioners will approach them and explain that their team is participating in the trial and that they are also invited to do so.

#### Consent process

During a site set-up visit to each TMCD the AQUEDUCT research team will take consent from the two TMCD practitioners acting as research coordinators. These research coordinators will arrange and confirm consent with their fellow TMCD practitioners, following the procedure used for confirmation of their own consent. This delegation of responsibility will be recorded formally in the Site Delegation Log.

People with dementia and carers will be approached by TMCD practitioners and given an information sheet, opportunities to ask questions and up to 3 days to decide if they wish to participate. If they agree, formal consent will be obtained from the person with dementia. This consent will be seen as a continuing process and at each meeting, the practitioner will determine their capacity (according to the Mental Capacity Act 2005 [24]) to give informed consent to take part in the research. A consent form will be completed separately with the carer regarding their involvement in the trial.

All participants will be informed of their right to withdraw from the research for any reason and at any time and that this decision will not impact on their current or future work within clinical services or access to and use of services. In certain circumstances, the CI may withdraw people with dementia from the trial if it is no longer considered to be in their best interest to continue.

### Outcome measures

The schedule of outcome measures and assessment points is provided in the SPIRIT chart (Fig. 3).

**Fig. 3 Fig3:**
[figure not shown]
Schedule of enrolment, interventions, and assessment points

#### Primary outcome measure

##### Psychiatric hospital admissions for people with dementia

All psychiatric hospital admissions for people with dementia from the TMCD catchment area (as defined by post codes) will be collated and reported at baseline and 6-month follow-up point for the preceding 6-month period.

#### Secondary outcome measures for people with dementia

##### Acute/general hospital admissions for people with dementia

All acute/general hospital admissions for people with dementia from the TMCD catchment area (as defined by post codes) will be collated and reported at baseline and 6-month follow-up point for the preceding 6-month period.

#### Secondary outcome measures for people with dementia and their carers

##### Service satisfaction (one measure)

The Client Satisfaction Questionnaire (CSQ-8) is a brief satisfaction with service measure and consists of eight items designed to measure satisfaction with health and human services in a single scale [25].

##### Quality of life and psychological wellbeing (two measures)

The EuroQol 5-dimension 5 level questionnaire (EQ-5D-5 L) is a brief assessment of the quality of life which comprises five dimensions: mobility, self-care, usual activities, pain/discomfort and anxiety/depression each rated by five levels of severity [26, 27]. The General Health Questionnaire (GHQ-12) is a brief 12-item scale which measures current mental health and psychological well-being [28].

#### Secondary outcome measures for TMCD practitioners

##### Work environment (two measures)

The Work Acceptance and Action Questionnaire (WAAQ) assesses psychological flexibility in relation to the workplace and comprises seven items which rate ability or willingness to remain engaged in occupational work while experiencing distressing thoughts and emotions [29]. The Utrecht Work Engagement Scale (UWES) is a 17-item scale measuring three dimensions of work engagement (vigour, dedication and absorption) [30, 31].

##### Wellbeing in work (two measures)

The General Health Questionnaire (GHQ-12) is a brief 12-item scale which measures current mental health and psychological well-being [28]. Sickness absence is used as a common proxy for work wellbeing and will be collated for all TMCD practitioners for each team.

##### Fidelity Measure (one measure)

The Fidelity Measure is a measure of practice quality in managing crises and part of the Resource Kit developed from the AQUEDUCT research programme. It will be completed by each TMCD in the intervention arm only.

#### Cost measures

##### Resource use (five measures)

Psychiatric hospital admissions for people with dementia within the TMCD’s catchment area (as defined by post codes) will be collated and reported at baseline and 6-month follow-up point for the preceding 6-month period. Acute/general hospital admissions for people with dementia within the TMCD’s catchment area (as defined by post codes) will be collated and reported at baseline and 6-month follow-up point for the preceding 6-month period. A record of both the number of permanent care home admissions and respite care admissions from each TMCD during the intervention phase will be collated to indicate use of other high-cost resources. In the intervention arm only, staff time use in implementing the Resource Kit and support time given to staff for this will capture additional costs of the intervention. Cost information will be collected using a ‘reduced list’ approach to costing [32], reflecting the necessary parsimonious adaptation of methodology required following the COVID-19 pandemic. This will avoid the use of expensive-to-collect items of data which are unlikely to vary and affect overall cost differences between the intervention arm and TAU arm, such as GP costs.

#### Other data collected

##### Serious adverse events

In accordance with Good Clinical Practice all data collectors will report deaths and adverse events that are life threatening, require or extend hospitalisation, result in disability or incapacity or are otherwise significant. All adverse events will be recorded in the case report form.

### Procedure

Overall involvement in the trial will be for 8 months, to include: provision of hospital admission data from all NHS Trusts at baseline and 6 months follow-up; initial set-up; completion of the Fidelity Measure before and after implementation of the Resource Kit; and delivery of all participant-completed measures. TMCDs in the intervention arm will implement the Resource Kit for 6 months and TMCDs in the control arm will deliver TAU for 6 months.

#### Data collection

Data will be collected from NHS Trusts, TMCDs, team practitioners, and new referrals of people with dementia and carers to these TMCDs.

Psychiatric hospital admissions data in the TMCD catchment area will be collated and reported by the relevant NHS Trust Department retrospectively at baseline and at 6-month follow-up. Acute/general hospital admissions data from each TMCD catchment area will be collected from each hospital by the research team retrospectively at baseline and at 6-month follow-up. Each TMCD in the intervention arm will complete the Resource Kit Fidelity Measure at baseline and 6-month follow up to identify gaps in their practice.

TMCD practitioners in both arms of the study will complete three questionnaires (WAAQ; UWES; GHQ-12) at baseline and at 6-month follow-up point. Sickness absence will be collated at team level for all TMCD practitioners at baseline and at 6-month follow-up point for the preceding 6-month periods. In both study arms, practitioners will record the number of permanent care home admissions and respite care admissions throughout the intervention phase for those people with whom the TMCD has engaged. TMCD practitioners in the intervention arm only will keep activity records to monitor time spent implementing the Resource Kit during the research.

After discharge from the TMCD service, people with dementia and carers will be asked to complete three questionnaires (CSQ-8, EQ-5D-5 L and GHQ-12). All measures can be completed within 6 weeks of discharge from the TMCD.

#### Random allocation

Following consent, each TMCD will be entered onto a web-based randomisation system and be randomly assigned to one of two arms, either using the Resource Kit or TAU with equal opportunity. The allocation will be determined by a computer-generated pseudo-random code using random permuted blocks of varying size, minimised by the number of people with dementia admitted to psychiatric hospital in the previous 6 months (either classified as low if the number is less than 25, or high if 25 or more) in each TMCD catchment area. The block size will not be disclosed to the research team. The randomisation system was set up and managed by the Research and Innovation team at the University of Nottingham (separate from the research team) in accordance with their standard operating procedure and is held on a secure server. The randomisation process is described in detail in a separate file and held securely within the statistics master file.

### Masking

People with dementia, carers, statisticians, and the DMC will be blinded to TMCD arm allocation until the data analysis is completed. However, masking of TMCDs is not possible.

### Data management

Study data will be managed using REDCap electronic data capture tools (version 10.0.5 LTS) [33, 34] hosted at the University of Nottingham. All data will be treated in a confidential manner and in accordance with UK data protection legislation. All research staff and practitioners involved in the study will be appropriately trained and supported with regards to the collection, storage, processing and disclosure of personal information. Unmasked researchers will enter data into REDCap software in accordance with study-specific guidance. Each participant will be assigned a unique identification code that will be used for all research data linkage and storage systems to ensure anonymity. Participants’ identifiable information will be stored securely, separate from the anonymised research data. A full audit trail will be maintained by recording all amendments to data specifying reason and time. Personal data will only be accessible to the minimum number of individuals necessary for data analysis or audit. Data may be inspected and audited by the sponsor and research ethics committee. Study investigators will have access to the study data by request from the CI and only anonymised data will be transferred to co-investigators at other sites. Following completion of the study non-personal data will be stored for five years in accordance with the terms of the Sponsor’s contract with the funder and personal data will be stored for three to 6 months to allow completion of the research, and for results to be disseminated to participants if required.

### Sample size

Information collected in different stages of the AQUEDUCT research programme, showed the average hospital admission count per TMCD catchment area over a 6-month period to be between 17 and 33. Following stakeholder consultation, a 20% reduction represented the minimum clinically significant difference in outcome. Therefore, 15 TMCDs will be required in each of the two study arms (30 in total) to detect a 7-point mean admission count difference between arms with 90% power at a two-tailed 0.05 significance level, assuming the count of hospital admissions follows a Poisson distribution. Stata 16 software was used for this power analysis. It is anticipated that no TMCD will withdraw from the study and that NHS Trusts will provide the required hospital admissions data for each TMCD; thus, the number of TMCDs required is unlikely to be influenced by lost information due to withdrawal. However, to manage risk of loss, additional team sites will be kept in reserve.

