### Statistical analysis

The data analysis will be conducted on an intention to treat basis. The treatment effects estimate (95% CI) on the primary outcome and the number of general hospital admissions will be quantified using Poisson regression with binary arm status as an exploratory variable and the size of the population with dementia within each TMCD catchment area as an offset. An over-dispersion check will be performed, and a negative binomial regression model will be used if there is evidence that the outcome variance is greater than the mean. The treatment effect estimates on TMCD practitioners’ and people with dementia and carers’ outcome measures will be explored using multilevel modelling with the TMCD as a level two analytical unit and baseline measures included as covariates [35, 36]. Skewed continuous outcome variables will be transformed for multilevel modelling, and nonlinear multilevel modelling will be performed for categorical outcomes. No interim analysis is planned, and safety and adverse event information will be presented descriptively. Missing values will be imputed via analytical modelling assuming missing at random status. Stata 17 will be used to analyse the data.

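### The 90% power for a 20% reduction holds only near the top of the trial's own 17–33 range of mean counts, and only with no extra-Poisson variation between teams

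*Protocol article*

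**What the plan says.** All of the sample-size reasoning is in one paragraph of the protocol article (Sample size). It contains these elements:

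- Earlier stages of the programme gave average counts per team catchment of 17 to 33 over 6 months.
- After stakeholder consultation, "a 20% reduction represented the minimum clinically significant difference in outcome".
- Linked to this by the word therefore, 15 teams per arm are required "to detect a 7-point mean admission count difference between arms with 90% power at a two-tailed 0.05 significance level".
- The variance model is stated: "assuming the count of hospital admissions follows a Poisson distribution".

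The paragraph names no control-arm mean behind the 7 points and no between-team variance.

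Two other sections bear on the variance. Under Statistical analysis, the primary model is a Poisson regression with the catchment's dementia population as an offset, and "a negative binomial regression model will be used if there is evidence that the outcome variance is greater than the mean". Under Random allocation, teams are balanced on their previous 6-month count, "either classified as low if the number is less than 25, or high if 25 or more".

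**The concern.** The paragraph moves from a relative target (20%) to an absolute one (7 admissions) as if the second followed from the first. It can follow only for a particular control mean, and none is given. A reader will take it that 15 teams per arm give 90% power for the minimum important effect whatever the control mean turns out to be within 17 to 33.

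The power also rests on a variance equal to the mean, meaning that teams do not differ in true rate beyond what the model explains. The analysis section treats that as something to be checked, but the sample size has no margin for the check failing.

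At stake is how the primary result is interpreted. The trial has 30 randomised units. If the control mean is in the middle or lower part of the range, the chance of missing a real 20% reduction is well above the 10% that the stated power implies.

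**Working it through.** **Inputs.** From Sample size: two-sided alpha 0.05, power 90%, 15 teams per arm, a 7-point difference, a 20% target, control means of 17 to 33, Poisson variance. From Design: 1:1 allocation. Assumed, because the document gives no value: an extra between-team coefficient of variation, c, of 0, 0.1 or 0.2.

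**Formulas.** With control mean m1 and intervention mean m2 (normal approximation):

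- n per arm = (m1 + m2)(1.960 + 1.282)² / (m1 − m2)², where the squared term is 10.507
- power = Φ( (m1 − m2) / √[(m1 + m2 + c²m1² + c²m2²)/15] − 1.96 )

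**Step 1: reproduce the plan's figure.**

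- A 20% reduction from 33 is 33 to 26.4, a difference of 6.6, which rounds to 7. n = 59.4 × 10.507 / 6.6² = 14.3, so 15 per arm. Power with 15 = Φ(6.6/√(59.4/15) − 1.96) = Φ(1.357) = 91%. This matches the stated 15 teams and 90%.
- An alternative also fits: 35 to 28, with the control variance used in both arms, gives n = 2 × 35 × 10.507 / 49 = 15.01 and power 90.0%. But 35 lies outside the stated range and is not mentioned in the document.

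**Step 2: compare 7 points with the 20% target.** Twenty percent of 17, 25 and 33 is 3.4, 5.0 and 6.6. Seven points is 7/17 = 41%, 7/25 = 28% and 7/33 = 21%. It is exactly 20% only at 7/0.20 = 35.

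**Step 3: power for a true 20% reduction, 15 v 15 teams, Poisson variance (c = 0).**

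| Control mean | Difference | Power | Teams per arm for 90% |
|---|---|---|---|
| 17 | 3.4 | 66% | 28 |
| 20 | 4.0 | 73% | 24 |
| 25 | 5.0 | 82% | 19 |
| 30 | 6.0 | 89% | 16 |
| 33 | 6.6 | 91% | 15 |

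Simulation of the Wald test from a Poisson regression agrees: 66%, 82% and 91% at means 17, 25 and 33.

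The mean at which 15 per arm just gives 90% solves 1.8m × 10.507 / (0.2m)² = 15, so m = 1.8 × 10.507 / (0.04 × 15) = 31.5. The part of the range above this is (33 − 31.5)/(33 − 17), about 9%.

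**Step 4: reduction detectable with 90% power.** For a proportional reduction x, (2 − x)/x² = 15m/10.507. At m = 25 the right side is 35.7, which gives x = 0.223, about 22%.

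**Step 5: illustration of overdispersion.** Power for a 20% reduction with an assumed extra CV:

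| c | Mean 17 | Mean 25 | Mean 33 |
|---|---|---|---|
| 0 | 66% | 82% | 91% |
| 0.1 | 60% | 74% | 83% |
| 0.2 | 46% | 55% | 61% |

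For example, at mean 25 and c = 0.1 the variance sum is 25 + 6.25 + 20 + 4 = 55.25, and power = Φ(5/√(55.25/15) − 1.96) = Φ(0.645) = 74%.

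**The case against.** The strongest reply is that the figure is correct where it was calculated. At a control mean of 33, inside the stated range, a 20% reduction needs exactly 15 teams per arm and has 91% power, and 7 is a fair rounding of 6.6. This stands. A reader might infer from 7 being 20% of 35 that the calculation is simply wrong, or that the 90% never applies to a 20% reduction. The document does not support that. What it shows is a planning mean that is unstated and appears to be the most favourable one available.

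A second reply concerns overdispersion, and much of it stands too. The document gives no between-team CV, so the lower rows of the last table are illustration and not estimates. The range 17 to 33 is described as averages from different stages of the programme, so it is not a between-team spread. The cut at 25 divides raw counts, which depend partly on catchment size, and the population offset may absorb part of that variation. The negative binomial model is conditional, a safeguard and not a forecast. A reader might conclude that the trial's real power is about 50%; the document cannot establish that. What remains is that the stated power has no margin if the safeguard is needed.

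Third, a reader might fear that a null result will be taken to rule out a 20% reduction. The protocol does not say so, and it commits to an effect estimate with a 95% confidence interval, which shows what is excluded whatever the planned power. That limits the harm but does not make the stated power correct. None of these replies changes the Poisson results at 17 and 25, which use only the protocol's own inputs.

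The article may condense a fuller protocol that names the control mean. Even so, the inference from 20% to 7 points is stated here, and it does not hold across the range given here.

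**Conclusion.** Wrong as written, within limits. The 90% power for a 20% reduction is valid at control means of about 31.5 or more and with zero extra-Poisson variation. Over the rest of the 17 to 33 range it is lower: 82% at 25 and 66% at 17, where the trial would miss a true 20% reduction about one time in three. These figures rest only on the protocol's inputs and a normal approximation that simulation confirms. Any overdispersion left after the offset lowers them further, by an amount that this document cannot fix.

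**What to change.** Keep 30 teams and rewrite the Sample size paragraph to:

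- name the control mean from which the 7 points was derived;
- express the target as a rate ratio of 0.80, and stop presenting 7 points as the 20% minimum important difference across the range;
- give power at control means of 17, 25 and 33 under Poisson variance, and again under a negative binomial variance, with the dispersion estimated from the programme's earlier data or the baseline counts (with the same population offset, so that only residual variation counts);
- state the reduction that 15 teams per arm can detect with 90% power, about 22% at a mean of 25 under Poisson.

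This changes wording and needs a short calculation on counts that the programme already holds or will collect at baseline. It adds no teams and does not alter the design or the primary model. It also does not raise power: the cost is that the stated power becomes less favourable.

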### Statistical analysis

The data analysis will be conducted on an intention to treat basis. The treatment effects estimate (95% CI) on the primary outcome and the number of general hospital admissions will be quantified using Poisson regression with binary arm status as an exploratory variable and the size of the population with dementia within each TMCD catchment area as an offset. An over-dispersion check will be performed, and a negative binomial regression model will be used if there is evidence that the outcome variance is greater than the mean. The treatment effect estimates on TMCD practitioners’ and people with dementia and carers’ outcome measures will be explored using multilevel modelling with the TMCD as a level two analytical unit and baseline measures included as covariates [35, 36]. Skewed continuous outcome variables will be transformed for multilevel modelling, and nonlinear multilevel modelling will be performed for categorical outcomes. No interim analysis is planned, and safety and adverse event information will be presented descriptively. Missing values will be imputed via analytical modelling assuming missing at random status. Stata 17 will be used to analyse the data.

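### The primary admissions model leaves out the baseline admission rate, which every team supplies; the analysis is valid but gives up precision if teams differ persistently beyond catchment size

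*Protocol article*

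**What the plan says.** Under Statistical analysis, the Protocol article specifies the model for psychiatric admissions (primary) and general hospital admissions as "Poisson regression with binary arm status as an exploratory variable and the size of the population with dementia within each TMCD catchment area", with population size entering as an offset. If the counts are over-dispersed, a negative binomial model replaces the Poisson model. No covariate is added in either case.

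The baseline value of the primary outcome exists for every team. Under Primary outcome measure, psychiatric admissions from the catchment area "will be collated and reported at baseline and 6-month follow-up point for the preceding 6-month period". Acute/general admissions are collected on the same schedule. Under Random allocation, the allocation is "minimised by the number of people with dementia admitted to psychiatric hospital in the previous 6 months", classed as low below 25 and high at 25 or more.

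For the practitioner, patient and carer outcomes, the same Statistical analysis paragraph does name baseline adjustment: "multilevel modelling with the TMCD as a level two analytical unit and baseline measures included as covariates".

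**The concern.** There are only 30 units of analysis. The offset removes differences in the size of the dementia population. It does not remove lasting differences in admission propensity, such as those due to bed supply or service model. Under Recruitment the plan deliberately seeks varied service models, so such differences are plausible, and the negative binomial fallback shows that extra variation is anticipated. That fallback widens the interval to reflect the variation but explains none of it. The previous period's admission rate is the obvious variable to explain it. It is known before allocation and needs no new data. Allocation on a two-level split also leaves imbalance within each level. What is at stake is power and the width of the confidence interval for the primary outcome.

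**Working it through.** **The plan's own figure.** Sample size asks for 15 teams per arm "to detect a 7-point mean admission count difference between arms" "with 90% power at a two-tailed 0.05 significance level", with Poisson counts. The control mean used is not stated; the section gives the "average hospital admission count per TMCD catchment area over a 6-month period to be between 17 and 33". Taking 33 against 26:
- n = (1.96 + 1.2816)² × (33 + 26) / 7² = 10.51 × 59 / 49 = 12.7, so 13 per arm.
- With a t reference, 14 per arm.
- With a common SD of √33, 2 × 33 × 10.51 / 49 = 14.2, so 15 per arm.

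The stated 15 therefore reproduces near the top of the range, with no between-team variation and no covariate.

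**Inputs for the gain.** 15 teams per arm (plan). A 20% reduction (plan: "a 20% reduction represented the minimum clinically significant difference in outcome"). Control mean 25, the midpoint of 17 and 33. Between-team CV of the rate after the offset, and persistence (the correlation of a team's underlying log rate between periods), are not in the document. They are **assumed** at 0 to 0.4 and 0.5 to 0.9.

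**Formulas (log scale).**
- Between-team variance: s² = ln(1 + CV²)
- Unadjusted variance per team: v = s² + (1/25 + 1/20)/2 = s² + 0.045
- Variance of the baseline log rate: vb = s² + 1/25
- Adjusted variance: v − (persistence × s²)² / vb
- Power = Φ(ln(1.25)/√(2v/15) − 1.96), with ln(1.25) = 0.223

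**Worked case, CV 0.3, persistence 0.7.** s² = 0.0862 and v = 0.1312. SE = √(2 × 0.1312/15) = 0.132, so power is 39%. The variance explained is (0.7 × 0.0862)² / 0.1262 = 0.0288. Adjusted v = 0.1023 and SE = 0.117, so power is 48%.

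| CV | Unadjusted | Persistence 0.5 | 0.7 | 0.9 |
|---|---|---|---|---|
| 0 | 82% | 82% | 82% | 82% |
| 0.2 | 56% | 58% | 61% | 65% |
| 0.3 | 39% | 43% | 48% | 56% |
| 0.4 | 28% | 33% | 38% | 49% |

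**Why the rate and not the count.** Log count = log population + log rate. The offset already fixes the population coefficient at 1. Log count beside it brings size in again, so its coefficient is pulled towards zero as sizes vary. Take a catchment-size CV of 0.5 (assumed), which has log-scale variance ln(1.25) = 0.223. At CV 0.3 and persistence 0.9, (0.9 × 0.0862)² = 0.0060. With the rate, the variance explained is 0.0060/0.1262 = 0.048. With the count it is 0.0060/(0.1262 + 0.223) = 0.017, about a third as much. The table therefore applies to the rate, or to equal-sized catchments.

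**Simulation.** 30 teams, allocation stratified at 25, means 25 against 20, catchment-size CV 0.5:
- CV 0.2, persistence 0.7: 53% unadjusted, 54% with log rate.
- CV 0.3, persistence 0.7: 38% unadjusted, 43% with log rate.
- CV 0.3, persistence 0.9: 36% unadjusted, 51% with log rate, 38% with log count.
- CV 0: 76% unadjusted, 74% adjusted.

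These figures carry Monte Carlo error of a point or two.

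**The case against.** **No validity problem is shown.** This stands. Randomisation keeps the unadjusted estimate unbiased, and the fallback allows for over-dispersion. Because the allocation factor is omitted, a reader might infer that the primary test is invalid or inflates false positives. The checks do not support that. In stratified simulations under the null, the unadjusted model rejected in about 5% of runs (1.8% to 8.2% across settings of 400 runs each). A longer run of 1,500 at CV 0.3 and persistence 0.8 gave 3.7-4.1%, which is mildly conservative if anything.

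**The size is assumed.** This also stands. The plan's own power calculation assumes Poisson counts, and under that assumption adjustment gains nothing. A reader might also infer that between-team variation dominates the error. At CV 0.2 it does not: s² = 0.039 against a Poisson term of 0.045.

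**Stratified allocation already captures part of the benefit.** This is true. In simulation with equal-sized catchments and persistence 0.7-0.9, the actual variance of the estimate fell by 2-3% at CV 0.2 and 8-17% at CV 0.3. The formula gives 11-19% and 22-36%. Much of the power gain comes from a standard error that better matches the estimate's true spread.

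**Adjustment may be left to the analysis plan.** The Economic evaluation section does refer adjustment to that plan, and the model sentence does not rule out further terms. This carries limited weight. The article lists the terms of the admissions model and, in the same paragraph, names baseline covariates for the other outcomes. Read as written, the admissions model has none.

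**Conclusion.** The point holds as an inexpensive gain in precision. The stated model for both admission outcomes omits a baseline measure that is collected for every team and, for psychiatric admissions, already used in allocation. If teams differ persistently beyond catchment size, power is given up. By the formula, at persistence 0.5 to 0.9 the gain is 2-9 points at CV 0.2, 4-17 at CV 0.3 and 5-21 at CV 0.4. With stratified allocation and unequal catchments, simulation gives from about 1 point (CV 0.2, persistence 0.7) to about 15 (CV 0.3, persistence 0.9). If variation is purely Poisson there is no gain, and 1-2 points are lost.

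The direction is secure wherever persistent team differences exist. The size rests on an assumed CV, persistence and spread of catchment sizes, none of which the document gives. Adjustment also does not restore 90% power in any over-dispersed case tabulated (CV 0.2 to 0.4).

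**What to change.** Before unblinding, pre-specify the following:
- Add the log baseline 6-month admission rate (baseline count divided by dementia population, with a small constant added if any count is zero) as a continuous covariate in both the Poisson and the negative binomial model.
- Keep log dementia population as the offset. An acceptable alternative is log baseline count together with log population as a free covariate in place of the offset.
- Do not enter log baseline count beside the population offset.
- State whether the continuous rate replaces the low/high allocation factor or is added to it.
- Use the same form for acute/general admissions, with their own baseline rate.

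The cost is a sentence or two in the plan and one or two of the 28 residual degrees of freedom (30 teams less intercept and arm). No new data are needed.
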